**Fig. 2 Fig2:**
[figure not shown]
Schematic of study design

Observer bias will be reduced where feasible. However, there are limits because the material of each type of net is distinct to touch. Manufacturers’ labels will be removed before distribution and nets allocated using a unique nine-digit numerical identification (ID) code, composed of village (3), hamlet (2), household (3) and net (1) numbers, stenciled directly onto the LN using permanent dye. Separate IDs will be issued to those LNs assigned to the cohort study. Technicians conducting the bioefficacy, fabric integrity assays and survivorship surveys will be blinded to the brand of LN.

During destructive sampling, it is important to replace LNs with nets of the same brand to measure the true rate of loss of fabric integrity. For example, households using a specific LN may prefer another type of net given freedom of choice and use that in preference to any of the former nets still present in the house. This could result in nets of the former type developing holes less rapidly and appearing artificially more ‘durable’, thereby introducing an avoidable bias.

Fabric integrity will be assessed using two methods, by following a longitudinal cohort and cross-sectional surveys. This should detect any potential user bias resulting from the ‘Hawthorne effect’, the possibility that regular visits render participants more inclined to retain or care for their nets and less likely to dispose of them when damaged because they are being observed.

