**Methods:**

This is a prospective three-arm household randomized, equivalence trial of LNs in Tanzania, with nets as the unit of observation. Equal numbers of houses will be randomized to receive deltamethrin-treated polypropylene, polyester or polyethylene LNs; all sleeping spaces in a given household will be provided with one type of net. Bioefficacy (insecticidal activity against mosquitoes), insecticide content of net fibres, and fabric integrity (number, location and size of holes) will be measured every 6 months, using WHO cone or tunnel bioassays, chemical analysis and calculation of hole index, respectively. A cohort of LNs will be surveyed annually to assess survivorship (median LN survival time) and cumulative loss of fabric integrity. Field durability outcomes will be compared with laboratory strength tests.

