### Study design, randomization, blinding and bias

This will be a prospective cluster randomized controlled, equivalence trial with nets as the unit of observation. Following household enumeration, global positioning system (GPS) coordinates will be recorded and baseline socio-demographic and economic data, including age, sex, occupation, education, household wealth, sleeping habits and number of spaces, ownership and use of other mosquito nets and net preferences (size, colour, shape and washing habits) will be collected using a standardized questionnaire.

Once baseline chemical analysis of LNs is completed and confirmed to be within WHO specifications, the nets will be distributed. The monitoring period will be 3 years, beginning August 2014 (Table 1). At study onset, equal numbers of households from eighteen hamlets will be randomized to the three study arms. All participating households in a specific hamlet will be provided with the same type of LN to achieve universal coverage, assuming an average of 4.0 sleepers and 2.1 sleeping places per household. To ensure all members in a participating household are using the same LN brand, any existing nets will be removed and replaced by study LNs. All LNs will be issued free of charge to recipients. Net users will be encouraged to retain the LNs they are given and not to sell or exchange them with other study participants. If for any reason an owner stops using a net, they are requested to volunteer the reason and to store the net for later inspection by investigators.

**Table 1 Tab1:** Timetable of study activities

Activity	Pre-Intervention	Post Intervention monitoring period (months)						
		0	6	12	18	24	30	36
Community selection, sensitization and consent	X							
Baseline census and household survey	X							
LLIN distribution	X							
Cross-sectional surveys: bioefficacy assays	X	X	X	X	X	X	X	X
Cross-sectional surveys: chemical assays	X			X		X		X
Cross-sectional surveys: fabric integrity		X	X	X	X	X	X	X
Cross-sectional surveys: fabric strength		X	X	X	X	X	X	X
Cross-sectional surveys: community practices		X	X	X	X	X	X	X
Cohort surveys: household survivorship and fabric integrity		X	X	X		X		X
Insecticide resistance monitoring	X			X		X		X
Adverse events monitoring		X						

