### Cross-sectional surveys: bioefficacy

To determine the insecticidal efficacy of each intervention, at the beginning of the study (t0) and every 6 months thereafter (t6, 12, 18, 24, 30), 30 LNs of each brand will be randomly selected from the net master list and assessed using standard WHO cone bioassays [8]; 50 LNs of each brand will be drawn randomly for the survey at 36 months (t36). LNs will be removed from participating households and replaced with new nets of the same type.

From each LN, five samples (25 × 25 cm) will be cut at positions 1 to 5 (Fig. 3). All bioassays will be performed using 2–5 day old non-blood fed, laboratory-reared susceptible *An. gambiae s.s.* Kisumu strain. Twenty mosquitoes will be exposed to each netting sample, in four standard WHO cones fixed with a plastic manifold, for 3 min and then held for 24 h in paper cups with cotton wool soaked with 10% sugar solution; knock-down will be recorded after 60 min and mortality after 24 h. Mosquitoes exposed to an untreated net will be used as a negative control in each round of assays. All bioassays will be performed at 25 ± 2 °C and 75 ± 10% relative humidity.

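### Hole scoring and survivorship are stated to be blinded to net brand, which the design cannot deliver; for mosquito scoring, blinding is achievable but no masking procedure is described

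*Protocol article*

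**What the plan says.** All of the following is from the protocol article.

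- **Blinding.** The section on study design, randomization, blinding and bias is the one concerned; its statement reads "Technicians conducting the bioefficacy, fabric integrity assays and survivorship surveys will be blinded to the brand of LN". Just before it, the section says that observer bias will be reduced where this is feasible, and adds "However, there are limits because the material of each type of net is distinct to touch". Manufacturers' labels are removed before distribution.
- **Net ID.** Each net carries a nine-digit code "composed of village (3), hamlet (2), household (3) and net (1) numbers, stenciled directly onto the LN using permanent dye". Cohort nets receive separate IDs whose format is not given.
- **Allocation.** The same section says "All participating households in a specific hamlet will be provided with the same type of LN to achieve universal coverage", and that "equal numbers of households from eighteen hamlets will be randomized to the three study arms". The abstract instead says "This is a prospective three-arm household randomized, equivalence trial of LNs in Tanzania, with nets as the unit of observation".
- **Appearance.** Table 2 gives the polyester net as blue, and the polypropylene and polyethylene nets as white.
- **Hole scoring.** In the cross-sectional fabric integrity section, each net is draped over a frame, and its holes are counted and sorted by size, cause and location.
- **Survivorship.** In the cohort section, the presence, hanging and loss of nets are recorded at household surveys, with reasons for loss. Under Data analysis, a net must be in use for sleeping to count as surviving, and a net kept but unused because of poor integrity counts as lost.
- **Cone test.** Mosquitoes are exposed "for 3 min and then held for 24 h in paper cups"; knock-down is read at 60 minutes and mortality at 24 hours.

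**The concern.** Blinding of assessors is a claim about procedure, and readers will use it to judge how far to trust the hole index and survivorship comparisons. Both depend on judgement: which size class a hole falls in, what caused it, whether a net is in use, and whether it was given up for wear or for another reason. An assessor who knows the brand, and perhaps the manufacturer's claim of better durability reported in the Background, could be influenced in these calls.

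The Discussion says the trial is primarily designed to compare relative field durability, so the claim is weakest on the outcomes that matter most. If it stands uncorrected, the durability results may be reported as blinded when they were not. For bioefficacy the issue is smaller: blinding is promised and can be achieved, but the article does not say how.

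**Working it through.** No stated figure is in dispute, so the main check sets the passages against one another.

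**1. Can the assessor recognise the net?**
- Touch separates all three materials, by the protocol's own statement.
- Colour separates only the polyester net (blue) from the other two (both white).
- Removing labels changes neither.

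**2. Does each assessment expose the assessor to these cues?**

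| Assessment | What the assessor meets | Can brand be concealed? |
|---|---|---|
| Hole scoring | the whole net, draped and examined | no |
| Survivorship and use | the nets in the home, in a known hamlet | no |
| Cone scoring at 60 min and 24 h | mosquitoes, after 3 min on the netting | yes, if cups are coded and the scorer has not handled the netting |
| Tunnel scoring | mosquitoes, once removed from the tunnel | yes, on the same condition |

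**3. Does the ID reveal the arm?** The code includes the hamlet. If all households in a hamlet have one net type, the hamlet digits determine the arm, and knowing the type used in each of 18 hamlets is enough to decode every cross-sectional net. If households were randomized individually, as the abstract says, the hamlet digits would reveal nothing. This route is therefore conditional. It is not shown for cohort nets, whose ID format is unstated. Steps 1 and 2 do not depend on it.

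**4. How sensitive are the read-outs?**

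*Hole index.* Table 3 weights the four size classes 1, 23, 196 and 576. Moving one hole to the next class up changes a net's index by
- 23 − 1 = 22
- 196 − 23 = 173
- 576 − 196 = 380

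This shows only what one changed call does to one net. It says nothing about how often calls would change, or in which direction.

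*Cone mortality, as an illustration.* Positions 2–5 with 20 mosquitoes each give n = 4 × 20 = 80; the 80% criterion needs 0.80 × 80 = 64 dead. With X ~ Bin(80, p), P(X ≥ 64) under an assumed 3-point upward scoring shift is:

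| True mortality | No shift | 3-point shift |
|---|---|---|
| 70% | 0.03 | 0.10 |
| 78% | 0.39 | 0.65 |
| 80% | 0.57 | 0.81 |
| 90% | 0.998 | about 1.00 |

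With all five positions (n = 100, at least 80 dead), the values at 78% are 0.37 and 0.66, and at 80% they are 0.56 and 0.83. The document gives no basis for the 3 points. The figures treat mosquitoes as independent and concern one net on the mortality criterion alone, before the 95% knock-down alternative and the tunnel retest. They are not probabilities of a net's final classification, and the effect is nearly absent well away from the cut-off.

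**The case against.** Several points on the other side are sound.

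- **The limit is partly disclosed.** The section concedes that touch restricts what can be done about observer bias. It then claims blinding for all three assessments without saying which one is limited, so the caveat does not correct the claim.
- **The master list is restricted.** Under the section on data handling and record keeping, only the principal investigator and senior field investigators see the full net list. The hamlet digits therefore do not unblind a technician unless the hamlet allocation is learned some other way, for instance by recognising the nets. This weakens the ID argument but not the argument from touch, colour and home visits.
- **The randomization unit is unclear.** The hamlet-to-arm link rests on one of two conflicting descriptions.
- **A condensed article may omit laboratory coding.** A reader might infer from the missing procedure that mosquito scoring is unmasked. The document does not support that: it says bioefficacy technicians will be blinded, never says that cut pieces or cups carry the stencilled ID, and may leave coding to a fuller protocol.
- **The binomial figures could be over-read.** A reader might take them as the effect of failed blinding on the efficacy verdict. They rest on an assumed shift at the cut-off and ignore the two further routes to a pass.

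What remains is not an omission. The article claims blinding for two assessments that its own description of the nets and methods makes impossible to conceal.

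**Conclusion.** The blinding statement is wrong as written for fabric integrity and survivorship, and should be corrected. This conclusion rests only on the stated difference in feel, the colours in Table 2, and the described way in which nets are examined and surveyed. It holds under either description of the randomization unit.

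The ID route adds to the problem for cross-sectional nets if allocation was by hamlet and someone learns the allocation. It remains conditional until the two descriptions are reconciled.

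For cone and tunnel scoring there is no contradiction: blinding is stated and feasible, and only the means are not described.

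The size and direction of any bias in the durability comparisons cannot be estimated from the document. The practical consequence is how those results may be described, together with a cheap chance to secure masking where it is possible. The trial status is monitoring year 2, so the 36-month assays, on which the 3-year bioefficacy requirement turns, are still ahead.

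**What to change.** 1. Correct the blinding sentence: hole scoring and survivorship are not blinded to brand; mosquito scoring in the cone and tunnel tests is masked by code. Report the durability results accordingly.
2. Give each cut netting piece and each holding cup a random laboratory code that carries no village, hamlet or household digits, with the link file held by the data manager.
3. Have cone mosquitoes, and tunnel mosquitoes after removal, scored by code by someone who has not handled the netting.
4. Reconcile the abstract's household randomization with the one-type-per-hamlet allocation in the design section, and state whether cohort IDs contain the hamlet.

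The cost is small: a few corrected sentences, a random label list, a link file, extra labelling at each survey, and a scorer separate from the person who handles the netting. Sample size and assay procedures are unchanged.

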To assess bioefficacy (insecticidal activity measured by mosquito knock-down and mortality), deltamethrin content (g/kg and mg/m^2^), fabric integrity (location and size of holes) and fabric strength, a series of cross-sectional surveys and destructive sampling of LNs will be undertaken on randomly selected nets every 6 months for WHO cone bioassays, yearly for insecticide analysis using gas chromatography (GC), and physical integrity (hole index) every 6 months up to 18 months and then annually. A longitudinal cohort of LNs will be followed every 6 months to measure survivorship (net attrition rate) and loss of fabric integrity. Community attitudes and practices of LN use will be assessed every 6 months using the standard WHO LN durability monitoring questionnaire. Impact of the interventions on insecticide susceptibility of major malaria vectors will be evaluated each year in study villages and neighboring control areas. Study participants will also be monitored for possible adverse events during the first month post LN distribution using a structured questionnaire. A schematic representation of the trial is shown in Fig. 2.

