### Cross-sectional surveys: fabric integrity

At t6, 12 and 18 months post LN distribution, the 30 LNs destructively sampled for bioassays will be scored for physical integrity by draping the nets over a frame and counting the number and types (due to burning, tearing, split seams or animal damage) of holes of different sizes according to location on the net (top, upper side, lower side). Holes greater than 0.5 cm will be classified into the following categories: smaller than a thumb (0.5–2 cm); larger than a thumb but smaller than a fist (2–10 cm); larger than a fist but smaller than a head (10–25 cm) and larger than a head (>25 cm). At t24 and 36, physical integrity of the nets will be evaluated for a randomly selected sample of 100 LNs of each brand (including the 30 destructively sampled for bioassays). Net integrity (hole index, hole area and circumference) of each net type will be calculated as per WHO guidelines [28] (Table 3). In addition, any evidence of repairs and types of modification will be recorded.

**Table 3 Tab3:** LN hole size index

Hole Size Categories (cm)	Hole Diameter^a^ (*d;* cm)	Hole radius (*r* = *d/*2)	Hole Area^b^ (π**r* ^2^)	Hole Index^c^
0.5–2.0	1.25	0.625	1.23	1
2–10	6	3	28.28	23
10–25	17.5	8.75	240.56	196
>25	30	15	706.95	576

^a^Weights for each size category were estimated assuming that the average hole diameter was the midpoint in each category, except for the largest hole where the average diameter was assumed to be 30 cm

^b^The approximate area of an average sized hole from each category was estimated by assuming each hole was approximately circular

^c^Final weights for each size category were then estimated by dividing the area encompassed by a hole in the smallest size category (i.e. 1.23)

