### Cohort study: household survivorship and fabric integrity

To measure LN household survivorship and attrition, a longitudinal cohort of 250 LNs from 125 randomly selected households (two nets per household) will be followed at t6, 12, 18, 24, 30 and 36 months post LN distribution. At each time point, 150 of the LNs (the higher of the 2 ID codes per house) will be examined to measure the loss of fabric integrity over time (hole index, as above) and net hanging (net usage), and attrition (physical presence/absence of the nets) of all household LNs will be assessed. When a LN is missing from a house, the participants will be questioned to determine the reason for its loss or absence, which will be categorised as: loss by giving away the LN to others, sold, stolen, mislaid, using for alternative purposes or discarded due to loss of integrity (wear and tear); the latter is most important for assessing the relative durability of each type of net. LN owners will be requested to retain and store the net if they stop using it and to allow its inspection during follow up surveys. At the end of the 3 year trial period, study nets will be replaced on their production regardless of condition. Study LNs in the house that have never been used will be recorded but excluded from the analysis.

In contrast to the cross-sectional surveys, where only surviving LNs will be examined, the cohort study will allow gradual deterioration of individual LNs to be monitored, and the point at which the net is discarded or no longer used, determined. Households participating in the cohort study will not be sampled during cross-sectional surveys.

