### Data analysis

All statistical analyses will be performed using STATA version 13 (StataCorp LP, College Station, TX, USA).

Bioefficacy data from the WHO cone tests will be used to calculate proportional knock-down and mortality. Bioefficacy results from the netting pieces of each LN will be pooled to determine whether the net meets the WHO efficacy criteria of ≥80% mortality or ≥95% knockdown. Bioefficacy data from the WHO tunnel tests will be used to determine whether nets that fail the cone test meet the WHO efficacy criteria of ≥80% mortality or ≥90% blood-feeding inhibition. Blood-feeding inhibition will be assessed by comparing the proportion of blood fed females (alive or dead) in treated and control tunnels. Overall mortality will be measured by pooling the immediate and delayed (24 h) mortalities of mosquitoes from the two sections of the tunnel, relative to the control. Mortality data in both WHO cone and tunnel tests will be corrected for negative control mortality using Abbott’s formula.

A candidate LN product must achieve the WHO requirement of at least 80% of sample nets meeting the bioefficacy criteria in the WHO cone bioassays or tunnel tests after 3 years of use.

Chemical analysis results will measure the mean (and standard deviation) target deltamethrin concentration in each type of LN to assist interpretation of the bioefficacy data. Insecticide content reported at each survey time will be used to estimate the average rate of insecticide loss from the original loading dose.

LN survivorship will be measured at each timepoint as the total number of each LN present in surveyed households (and used for sleeping under) divided by the total number of each LN originally distributed to households and not given away at each time point [6]. Median LN survival is the time point at which the estimate of functional LN survival reaches 50%. LN attrition is derived from the total number of LNs missing from each household (classified into categories of nets that have been destroyed or disposed for reasons other than poor fabric integrity, nets used for other purposes and nets destroyed for reasons of poor fabric integrity) divided by the total number of each LN distributed to households. LNs retained for inspection but no longer used for reasons of poor integrity will be included among the nets lost to attrition.

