WHOPES Phase III bioefficacy guidelines for LNs are currently based on retention of bioefficacy rather than physical durability. To obtain a WHOPES full recommendation at least 80% of the LNs surviving 3 years of household use in malaria endemic countries must retain sufficient insecticidal activity to induce 80% mosquito mortality in bioassay tests [28]. Four brands of LN have already achieved this criteria: polyester nets, PermaNet 2.0® and Interceptor® [35, 40], and polyethylene nets, Olyset® and DuraNet® [41, 42]. A further four LNs have obtained WHO full recommendations on the basis of equivalence to the aforementioned brands, and a further eight have obtained WHO interim recommendation after demonstrating bioefficacy in Phase II experimental hut trials [25]. While most brands of LN may achieve the requisite levels of bioefficacy, it is much less clear whether all types of net can physically withstand the wear and tear of 3 years of household use. LN survival will depend on the environment and household conditions of use. A LN stretched over a rustic wooden bed in a cramped traditional mud house will not last as long as a properly fitted LN draped over a bespoke net frame in a rodent free home. The duration of the mosquito season will also affect LN longevity and usage, and this will differ between the tropics and subtropics, highlands and lowlands, and coastal and plain areas [4, 15]. In practice, few brands of LN have undergone rigorous longitudinal monitoring. The first LNs to obtain WHOPES full recommendation - polyester PermaNet 2.0® LN and polyethylene Olyset® LN - were the subject of annual cross-sectional surveys of random samples of nets [35, 42] across a number of countries after 1–3 years of use rather than longitudinal monitoring of a documented cohorts of nets [28]. In these surveys it was noted that net integrity (hole index) reached a steady state after 2 years of use indicating that LNs with higher hole indexes were being discarded and not surviving to 3 years. In these countries only one brand of net had been distributed. Unless different types of LNs are tested in the same location, in parallel, in household randomized trials, it will be difficult to determine their relative durability under field conditions. Few LN brands have been evaluated against one another in this way. A recent exception was a household randomized trial in Cambodia between polyethylene Netprotect® LNs and polyester PermaNet 2.0® LNs [43]. Net survivorship exceeded 90% in the first 2 years but after 3 years decreased to ~60% for both LNs, indicating that nets of either material were unable to last much longer than 2 years. It is therefore appropriate that the proposed trial of a longer lasting polypropylene LN is assessed alongside and against polyester and polyethylene LNs over 3 years of field use.

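### Similar hole indices in cohort and cross-sectional nets would not rule out a Hawthorne effect, because better care and longer use of damaged nets push the index of surviving nets in opposite directions

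*Protocol article*

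**What the plan says.** In the protocol article, the section on study design, randomization, blinding and bias (after the Fig. 2 caption) states: "Fabric integrity will be assessed using two methods, by following a longitudinal cohort and cross-sectional surveys. This should detect any potential user bias", meaning the Hawthorne effect. The same sentence describes observed users as "more inclined to retain or care for their nets and less likely to dispose of them when damaged". The effect as defined therefore has two parts, care and retention.

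The cohort section separates the two components: "In contrast to the cross-sectional surveys, where only surviving LNs will be examined, the cohort study will allow gradual deterioration of individual LNs". Cohort households are kept out of the cross-sectional surveys. Survivorship belongs to the cohort: "A longitudinal cohort of LNs will be followed every 6 months to measure survivorship (net attrition rate) and loss of fabric integrity". Table 1 lists it only in the cohort row, and the cohort paragraph of the sample size rationale agrees.

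The cross-sectional fabric section scores 30 nets per arm at 6, 12 and 18 months. At 24 and 36 months, "physical integrity of the nets will be evaluated for a randomly selected sample of 100 LNs of each brand". It also records repairs.

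Data analysis adds: "LNs retained for inspection but no longer used for reasons of poor integrity will be included among the nets lost to attrition". The Discussion reads an earlier plateau in hole index as a sign that "LNs with higher hole indexes were being discarded and not surviving to 3 years".

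**The concern.** The two parts of the defined effect act on the compared quantity in opposite directions. Care means fewer holes in the nets still present. Less disposal means that badly holed nets stay among those present, which raises the average. The article recognises the second mechanism when it explains the earlier plateau.

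The cohort can separate hole growth from discard, because it follows each net. The cross-sectional side has only the hole scores of survivors, so the retention part has nothing to be compared with. Equal hole indices may mean no effect or two effects that offset.

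At stake is how cohort attrition and median survival are read. This comparison is the only check the article names for user bias in the cohort, and the Discussion hopes the trial will help define a median-survival criterion for nets. A reassuring null could be taken as evidence that observation did not lengthen net life.

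**Working it through.** The article gives no power or effect size for this check, so there is no stated figure to reproduce. The direction argument follows from the text alone. The numbers below only illustrate how large the masking could be.

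**Inputs from the article**
- Attrition allowance of 20% per year: 0.8³ = 51.2% still present at 36 months.
- Share of losses due to damage: 1/3 (the Cambodian trial in the Discussion, with twice as many other losses) to 32/84 = 38% (the earlier Tanzanian evaluation, 32% failed on integrity and 52% absent for other reasons).
- Nets pooled over three arms: cross-sectional 3 × 30 = 90 at 6 and 12 months, 3 × 100 = 300 at 24 and 36 months. Cohort 3 × 150 = 450 for holes and 3 × 250 = 750 for attrition. These are the follow-up visits at which both components score holes under every version of the schedule.

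**Assumed inputs**
- 30% of survivors badly damaged at 36 months without observation (range 20-40%).
- Observation halves the discard rate of damaged nets (range 25-75% reduction).
- Observation slows damage by 20% (range 10-30%).
- No clustering and no cohort losses in the hole comparison, both of which favour the check.

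**Model.** Nets are intact, badly damaged or lost, with yearly rates d (damage), q (discard of damaged nets) and o (other loss):
- I(t) = exp(−(d+o)t)
- D(t) = d[exp(−(d+o)t) − exp(−(q+o)t)]/(q − d)
- Survival = I + D; damaged share = D/(I + D)

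Calibration gives d = 0.198-0.209, q = 0.428-0.479, o = 0.144-0.133. Check at the first set, t = 3: I = 0.358, D = 0.154, survival 0.512, damaged share 0.300. Under observation (d × 0.8, q × 0.5): I = 0.404, D = 0.176, survival 0.580, damaged share 0.304.

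| Month | Damaged share, unobserved | Damaged share, observed | Power of hole check |
|---|---|---|---|
| 6 | 8.5-8.9% | 7.2-7.6% | 8% |
| 12 | 15.0-15.5% | 13.3-13.9% | 8% |
| 24 | 24.1-24.4% | 23.0-23.7% | 6% |
| 36 | 30.0% | 30.4-31.0% | 5-6% |

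Power is for a two-sided 5% test of two proportions. Survival at 36 months rises to 58.0-58.9%, a gain of 6.8-7.7 points. Jointly over the four visits the power is 7% (7-11% over the 20-40% range).

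**Where the check does respond.** With no care effect, power at 36 months is 47-55%, and 84-91% if discard falls by 75%. With damage slowed by 30%, joint power is 10-50%, but mostly towards fewer holes, which signals care and not retention. Exact cancellation at 36 months needs damage slowed by 21-23% in the central case (9-33% across the ranges), so the central case lies close to it.

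**Other models.** A simulation using the Table 3 weights and a rank test, with discard halved and damage slowed by 10%, gave a gain of 6.7-6.8 points and 5-8% power at every visit. At 20% slowing, power at 36 months was 10-30%, towards fewer holes. A third model with net-to-net variation in hole rate (rate × 0.7, discard × 0.5) raised survival from 56% to 69% with a mean hole index ratio of 1.01. Less discard alone gave a ratio of 1.37; care alone (× 0.8) gave 0.84.

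**An attrition comparison.** Finding 300 nets at 51.2% survival means drawing 300/0.512 = 586 IDs. For 51.2% against 58.0-58.9%, 586 IDs v 750 cohort nets give 70-80% power, or 42-51% at an assumed design effect of 2. If discard falls by only 25%, power is 20-44%.

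**How close survivorship is to 50%.** Data analysis removes nets given away from the denominator. If a fraction g of non-damage losses were given away and s is the damage share of losses, survivorship = 0.512/(1 − g × 0.488 × (1 − s)). This is 51.2% at g = 0, 55-56% at g = 0.25, 60-61% at g = 0.5 and 73-76% at g = 1. The article does not give g.

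**The case against.** The strongest reply is that near-cancellation is a selected case. The behavioural rates are assumed, and where one behaviour dominates the check has real power. That stands, so it would be wrong to infer that the comparison can never detect the effect.

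A reader might also infer that observation could carry a net type that falls short of three years past the 50% mark. The documents do not support that. The 51.2% is a sample-size allowance compounded over three years, and survivorship as defined, without nets given away, would be higher by an unknown amount. Damaged nets stored unused already count as lost, so only damaged nets kept in use longer can inflate it.

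Nor is a biased comparison between polymers shown. All arms have the same cohort visits, and nothing indicates an effect that differs by net type.

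Care is not seen through holes alone: recorded repairs are a partial signal, as are the interviews on use and washing. They do not measure retention.

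A journal article may omit how absent nets are logged in the cross-sectional surveys. But it does say where survivorship is measured, and it makes the detection claim itself.

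Finally, an attrition comparison would not isolate observation. All users are asked to keep their nets ("Net users will be encouraged to retain the LNs they are given and not to sell or exchange them with other study participants"). The Discussion, however, describes the no-sale request as made before recruitment to the cohort, together with replacement only on production of the net, and the cohort section repeats the replacement offer. The incentive is not clearly shared by both components. This narrows what the added check can conclude without removing its value.

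**Conclusion.** The concern holds as a limit on what the check can show. The comparison may reveal a Hawthorne effect, but a null difference in hole index does not exclude inflated cohort survivorship. This rests only on the article's own definition of the effect, its restriction of cross-sectional surveys to surviving nets, and its placing of survivorship in the cohort.

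The size is illustrative. A gain of about 7 points in survivorship at 36 months could coexist with a change of about 1 point or less in the damaged share, under the assumed rates and before clustering. The consequence for median survival cannot be fixed from the documents, and the comparison between arms is affected only if the effect differs by net type.

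**What to change.** 1. For every originally distributed net ID drawn from the master list for a cross-sectional survey, record one outcome: present and used, stored unused, or missing with reason. Include IDs drawn but not found. Leave out replacement nets, which are younger.
2. Compare attrition (with the Data analysis definitions) and hole index between components as two separate checks, by visit, pooled over arms and allowing for clustering.
3. Report any attrition difference as the combined effect of cohort observation and any cohort-specific retention terms. State that power is modest under clustering, about 42-51% at an assumed design effect of 2 in the central scenario.
4. Reword the detection claim: the comparison may reveal user bias, but a null result does not exclude it.

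The cost is one code per ID and a small added analysis, with no extra nets. At 51.2% survival, finding 100 nets per arm at 36 months means about 195 IDs drawn per arm (100/0.512), or about 98 if 50 are to be found. The article reports the trial in its second monitoring year, so the coding can start at the remaining visits.
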